#### Statistical analyses

##### Baseline data

All baseline data are analysed descriptively and presented per group (experimental vs. control).

##### Primary efficacy endpoint

The hypothesis of differences between the two groups (experimental vs. control) concerning the post-interventional chair-rise time, is tested using an ANCOVA with chair-rise time at baseline, treatment group and study centre effects as explanatory variables. Analysis of the data is undertaken using the principle of "intention-to-treat" (ITT) which will be used as the official result of the study. Additionally, a secondary "per protocol" analysis is performed. Participants who abort the intervention are not invited for the final assessment. This will result in missing values. Missing values in both groups are each replaced by randomly selecting a change in chair-rise time from the control group and adding this difference to the baseline chair-rise time (see sample size calculation).

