**Methods/design:**

The study is designed as a randomised controlled trial. We plan to recruit 210 patients (≥ 70 years) in about 15 general practices.

The experimental intervention (duration 12 weeks)-a multidimensional home-based exercise programme-is delivered to the participant by an exercise therapist in counselling sessions at the general practitioner's practice and on the telephone. It is based on methods and strategies for facilitating behaviour change according to the Health Action Process Approach (HAPA). The control intervention-baseline physical activities-differs from the experimental intervention with regard to content of the counselling sessions as well as to content and frequency of the promoted activities.

Primary outcome is functional lower body strength measured by the "chair-rise" test. Secondary outcomes are: physical function (battery of motor tests), physical activity (step count), health-related quality of life (SF-8), fall-related self-efficacy (FES-I), and exercise self-efficacy (SSA-Scale).

The hypothesis that there will be differences between the two groups (experimental/control) with respect to post-interventional chair-rise time will be tested using an ANCOVA with chair-rise time at baseline, treatment group, and study centre effects as explanatory variables. Analysis of the data will be undertaken using the principle of intention-to-treat.

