#### Appraisal by participants

During the final telephone interview, participants who completed the intervention are asked to rate the programme (standardised questionnaire). The rating (on a scale) includes quality, content and frequency of programme actions (e.g. personal and telephone exercise consultations) as well as quality and content of materials (e.g. workbook). Additionally, participants are asked to rate the concept used to approach and support them through their GP's practice.

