#### (Serious) adverse events

During every encounter with the participant (either experimental or control intervention group), the exercise therapist assesses and documents all adverse events (AEs, any previously unknown or increasing symptom or disease of any participant) by a standardised report protocol. The therapist forwards all protocols with AEs (the same day, personally or via fax) to the GP, who judges: serious/not serious; related/not related to participation in the study; subject may not continue participation/subject may continue participation but has to pause completely for x days/subject may continue participation immediately but with restrictions for x days/subject may continue participation immediately without any restrictions. Adapting the ICH Guidelines on "Clinical Safety Data Management-Definitions and Standards for Expedited Reporting E2A" [112] to our intervention, a serious adverse event (SAE) is defined as "any untoward medical occurrence that [...] results in death, is life-threatening, requires inpatient hospitalisation [...]" or "results in persistent or significant disability/incapacity [...]".

Outcome assessors report SAEs to the GP on the same day, if they obtain the information during assessments at the practice.

SAEs are also independently reported by the GP using the standardised report protocol immediately after he/she obtains knowledge of them during routine consultations at the practice or via other information routes.

Protocols of adverse events that have been classified as "serious" by the GP are forwarded promptly by fax (secure receipt) to the SAE manager (who is affiliated to the Institute of General Practice and Family Medicine, University of Witten/Herdecke), who reviews the GP's judgements. AE protocols remain at the practice for monitoring purpose.

The Institute of General Practice and Family Medicine (University of Witten/Herdecke) collects all SAE protocols, analyses frequency and type of SAEs and provides summary reports to the Data Safety and Monitoring Board (DSMB) on a regular basis. In case of numerous occurrences of SAEs, the DSMB suggests that the study should be stopped.

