#### Sample size and power calculations

A feasibility study (single-arm interventional study [53]) has been conducted to allow for sample size/power calculation.

For sample size/power calculation- an ANCOVA (with chair-rise time at baseline, treatment group and study centre effects as explanatory variables and post-intervention chair-rise time as dependent variable) was used. It included the following steps and assumptions (unless otherwise noted, all numerical values were taken from the feasibility study):

1. Baseline chair-rise times were assumed to be normally distributed with mean 15.74 s and variance 25.09 s independent of group allocation.

2. The centre effect was modelled as a fixed normal random variable with mean 0 s and variance 1.59 s and added to the chair-rise time at baseline.

3. Post-intervention chair-rise times were assumed to be normally distributed with variance 25.09 s (again independent of group allocation) and correlated with baseline values (Pearson correlation of 0.78).

4. The difference in chair-rise time between the intervention and the control group at study end was assumed to be 2.0 s (improvement of 2.5 s in the intervention group and 0.5 s in the control group). This is a conservative assumption, as the feasibility study revealed an improvement of 2.93 ± 3.92 s for the intervention.

5. A drop-out-rate of 20% was assumed. This is a conservative assumption, because the feasibility study indicated an unadjusted drop-out-rate of 17% among participants who were able to perform the chair-rise test.

6. Missing values in both groups were each replaced by randomly selecting a change in chair-rise time from the control group and adding this difference to the baseline chair-rise time. This is a conservative approach, as it weakens the treatment effect of the intervention while simultaneously maintaining the control group effect.

Using these steps (1.-6.) the simulation (10,000 runs) with α = 0.05 revealed that 105 patients per group assure a power of 94.6%.

Making the even more conservative assumption that the correlation between chair-rise time at baseline and chair-rise time at study end is 0.7 instead of 0.78, the number of 105 patients per group still results in a power of 86.7%.

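### Participants who stop the programme are not invited to the final assessment, so the intention-to-treat result fixes their treatment effect at zero instead of measuring it

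*Protocol article*

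**What the plan says.** The abstract of the protocol article states: "Analysis of the data will be undertaken using the principle of intention-to-treat". Under Statistical analyses, Primary efficacy endpoint, the same principle gives the official result, with a per-protocol analysis as secondary. That section then sets two rules:

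- Follow-up: "Participants who abort the intervention are not invited for the final assessment. This will result in missing values".
- Imputation: "Missing values in both groups are each replaced by randomly selecting a change in chair-rise time from the control group", which is added to the participant's own baseline.

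Secondary endpoints are analysed in the same manner.

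Sample size and power calculations uses the same imputation and describes it as conservative. On the amount missing it says: "A drop-out-rate of 20% was assumed". The support given is that "the feasibility study indicated an unadjusted drop-out-rate of 17% among participants who were able to perform the chair-rise test".

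Three other sections bear on who stops:

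- (Serious) adverse events lets the GP rule, after an adverse event, that the "subject may not continue participation".
- Methods to prevent bias says that GPs and exercise therapists know the allocation.
- Reasons for discontinued intervention has the therapist record medical and non-medical reasons.

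The article describes no other way of obtaining the final chair-rise time of someone who has stopped.

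**The concern.** An intention-to-treat comparison asks how the groups differ as randomised, including people who give up. Stopping the programme is no reason to stop measuring, but here it leads by rule to no measurement.

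Stopping happens after randomisation and may be related to health. It may also depend on arm. One arm asks for exercises, goal setting and a daily log, while the other gives information on light daily activity. The GP and therapist, who are involved when someone stops, are not blinded.

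The imputation then gives every aborter a control-like change. If the experimental programme made someone slower and they stopped for that reason, their chair-rise result would be entered as a typical control change. Whether the imputation errs on the safe side depends on outcomes that the follow-up rule prevents anyone from seeing.

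**Working it through.** **Inputs**, all from Sample size and power calculations unless marked:

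- 105 per group; about 15 practices (Study overview)
- Baseline mean 15.74 s and variance 25.09; centre variance 1.59
- Baseline to post-intervention correlation 0.78, or 0.7 in the sensitivity case
- Improvement 2.5 s (experimental) and 0.5 s (control); drop-out 20%
- Two-sided α = 0.05 (sidedness is not stated, so this is an assumption)

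**1. The plan's own figure.** I simulated the six listed steps: 4,000 runs, 21 missing at random per group, ANCOVA on baseline, group and centre. Power was 95.0% at correlation 0.78 and 87.2% at 0.7 with the centre effect at both visits. It was 93.0% and 86.8% with the centre effect at baseline only. The article states 94.6% and 86.7%, so its figures reproduce.

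**2. Amount imputed.** 0.20 × 210 = 42, leaving 168 (80%) measured. At 17%, 0.17 × 210 = 35.7, or about 36.

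**3. What the planned analysis estimates.** Assume completers improve by 2.5 s and 0.5 s, and control aborters by 0.5 s. Experimental aborters are assigned 0.5 s, so the target is

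0.8 × 2.5 + 0.2 × 0.5 − 0.5 = 1.6 s.

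The simulated mean was also about 1.6 s.

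**4. What the as-randomised difference would be.** Let experimental aborters truly improve by x seconds (negative means worsening). The documents give no value for x, so a range is assumed:

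difference = 0.8 × 2.5 + 0.2 × x − 0.5 = 1.5 + 0.2x.

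The power columns are for measuring everyone, taken from repeated simulations of 3,000 to 5,000 runs.

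| x (s) | True difference (s) | Planned target (s) | Power, corr. 0.78 | Power, corr. 0.7 |
|---|---|---|---|---|
| 2.5 | 2.0 | 1.6 | 99% | 98% |
| 1.5 | 1.8 | 1.6 | 98% | 95% |
| 0.5 | 1.6 | 1.6 | 95% | 88–89% |
| −1 | 1.3 | 1.6 | about 82% | about 72% |
| −2 | 1.1 | 1.6 | 66–69% | about 55% |
| −3 | 0.9 | 1.6 | 42–45% | about 37% |

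The planned analysis rejects in about 95% of trials at correlation 0.78 in every row, because the aborters' true outcome never enters it. It understates the effect in the first two rows and overstates it in the last three.

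**5. False positives.** Suppose there is no treatment effect, so both arms improve by 0.5 s, with 20% drop-out in each arm. Control drop-out is random. Experimental drop-outs are the fifth with the highest propensity to stop, and that propensity has correlation r with a poor outcome given baseline (r is assumed).

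- Residual SD = √(25.09 × (1 − 0.78²)) = 3.13 s.
- The best 80% of a standard normal average 0.28 / 0.8 = 0.35 SD better than the whole, where 0.28 is the normal density at the 80% point.
- Spurious benefit = 0.8 × 0.35 × r × 3.13, which is 0.39 s at r = 0.45 and 0.62 s at r = 0.71.

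In simulation the planned analysis rejected in about 15% of trials at r = 0.45 and about 30% at r = 0.71. Measuring everyone gave about 5% in both. With random drop-out in both arms the planned analysis also held about 5%.

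**The case against.** The strongest defence is that the loss is disclosed, the same rule applies to both arms, and it is already in a power calculation that reproduces. Every randomised participant stays in the analysis, and setting the aborters' treatment effect to zero is a recognised cautious choice. Under random drop-out it does not inflate the type I error. All of this stands, and it limits the point to bias and to which effect is estimated. It does not answer the case where experimental aborters do worse than controls.

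A reader might infer several stronger things that the documents do not support:

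- **That the official result is mostly imputed.** On the article's figures about 80% of outcomes are measured.
- **That the rule causes the whole 20%, or that 20% is a ceiling.** It is a planning assumption for total drop-out. The article does not separate those who would still attend from those who would refuse or could not.
- **That the bias must favour the exercise programme.** The table in the working shows both directions.
- **That measuring everyone can never lower power.** It does so when aborters do worse than controls, because the true effect is then smaller. That is no reason not to measure.
- **That harms are hidden.** Adverse events and reasons for stopping are recorded and reported per group. The gap concerns the efficacy outcomes.

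The final interview also says that "participants who completed the intervention are asked to rate the programme". That rating is only descriptive and adds little here.

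**Conclusion.** The point holds in this limited form: a cheap improvement, because an avoidable rule works against the intention-to-treat result that the article declares official. About 42 of 210 primary outcomes at 20% drop-out (about 36 at 17%) would be control-group draws, and an unknown part of these could have been measured.

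The planned analysis targets 1.6 s, while the as-randomised difference runs from 2.0 s down to 0.9 s over the assumed range. This rests on control aborters changing by 0.5 s and on completers meeting the planning assumptions. The article's description of the imputation as conservative is right only if experimental aborters improve by at least 0.5 s on average.

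The false-positive rates of about 15% and 30% rest on an assumed link between poor response and drop-out in the experimental arm only. They show what is possible and do not forecast this trial. The stated sample size and power are not in error.

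**What to change.** Replace the no-invitation sentence with: *All randomised participants are invited to the T1 assessment whether or not they completed the intervention, unless they withdraw consent to follow-up.* Limit the imputation, for primary and secondary endpoints, to outcomes that still cannot be obtained. In the sample-size section, say that the imputation is conservative only if experimental drop-outs do no worse than controls.

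The cost is a short amendment and at most about 40 extra final visits and calls by assessors and interviewers already working in the trial. Some who stop will still decline. The Trial status section says that participant recruitment had not begun, so the change could have been made before any outcome was lost. Outcomes not collected cannot be recovered later. With everyone measured, power at correlation 0.78 stays at about 95% or more if aborters do at least as well as controls.

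### The official p-value rests on one random draw of control-group changes, and its standard error is right only when drop-out is equal in both arms

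*Protocol article*

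**What the plan says.** Under Statistical analyses, Primary efficacy endpoint, the protocol article makes the intention-to-treat ANCOVA (baseline chair-rise time, group, centre) the official result. Patients who abort the intervention are not called to the final assessment, so their outcome is missing by design. The remedy is: "Missing values in both groups are each replaced by randomly selecting a change in chair-rise time from the control group", with that change added to the patient's own baseline time. Neither repeated draws nor a variance adjustment is mentioned.

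Sample size and power calculations, step 6, uses the same rule and justifies it: "This is a conservative approach, as it weakens the treatment effect of the intervention while simultaneously maintaining the control group effect". With it, the protocol reports that "105 patients per group assure a power of 94.6" per cent, and at correlation 0.70 that "the number of 105 patients per group still results in a power of 86.7" per cent.

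The section on secondary efficacy endpoints analyses those endpoints in the same manner, so the rule carries over to them.

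**The concern.** At the planned 20% drop-out, 0.20 × 210 = 42 primary outcomes would come from a random number generator and then be counted as measured. Two things follow.

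- The estimate and p-value move with the draw. Two analysts who both follow the text exactly can reach opposite conclusions on the single confirmatory test.
- Control changes are used as donors in both arms, but the ANCOVA treats all 210 values as independent. Its standard error can be too small or too large, depending on which arm loses more patients.

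At stake are the reproducibility of the official result and whether its nominal 5% error rate holds.

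**Working it through.** **Inputs from the protocol article (Sample size and power calculations unless noted).** 105 per group; α = 0.05; baseline and post-intervention variance both 25.09; correlation 0.78 (0.70 as the alternative); improvements of 2.5 s and 0.5 s, so a difference of 2.0 s; centre variance 1.59; drop-out 20%.

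**Assumptions.** Two-sided test, since the hypothesis is one of differences; 15 practices of 14 patients, 7 per arm, from the approximate figures under Recruitment; drop-out completely at random. Any split of drop-out by arm is an illustration.

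**Step 1: reproduce the stated power.** Simulating steps 1–6 (10,000 runs) gives 94.6% at correlation 0.78 (93.2–94.7% depending on how the centre effect enters) against the stated 94.6%. At 0.70 it gives 87.3% (86.1–87.3%) against 86.7%. Both reproduce. The mean estimated effect is 1.6 s, as expected: (1 − 0.20) × 2.0 = 1.6.

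**Step 2: noise from the draw.** The variance of a change is s² = 2 × 25.09 × (1 − 0.78) = 11.04. With drop-out fractions pE (experimental) and pC (control), redrawing moves the estimated difference with

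SD = √[(pE + pC) s²/n] = √[0.40 × 11.04/105] = 0.205 s.

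The model standard error in Step 1 is 0.449 s, so the draw alone moves the t statistic by about 0.205/0.449 = 0.46. Simulation (300 trials, 150 redraws each) gives 0.46–0.49. The chance that two draws on the same data disagree on significance is:

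- planned assumptions: about 6% (repeated simulations gave 5–7%);
- correlation 0.70: 11–12%;
- correlation 0.78, true difference 1.5 s: about 17%.

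In one simulated trial chosen because it was borderline, p ran from 0.006 to 0.197 (5th to 95th percentile of draws), and 55% of draws were significant.

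**Step 3: the standard error.** Let E and C be the mean changes among completers. Imputed values in both arms have expectation C given the data, so the estimated difference is (1 − pE)(E − C) plus draw noise. Its variance is

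(1 − pE)² [s²/(n(1 − pE)) + s²/(n(1 − pC))] + (pE + pC)s²/n = (s²/n)[1 + pC + (1 − pE)²/(1 − pC)].

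The ANCOVA in effect assumes 2s²/n. The ratio of true to assumed standard error is therefore √{[1 + pC + (1 − pE)²/(1 − pC)]/2}. For example, at 10/30 it is √[(1 + 0.30 + 0.81/0.70)/2] = √1.229 = 1.11. The analytic type I error is 2[1 − Φ(1.96/ratio)].

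| Drop-out exp./control (%) | SE ratio | Type I, analytic | Type I, simulated |
|---|---|---|---|
| 20/20 | 1.00 | 5.0% | 4.8–5.4% |
| 15/25 | 1.05 | 6.2% | 6.0–6.4% |
| 10/30 | 1.11 | 7.7% | 7.9–8.0% |
| 25/15 | 0.95 | 3.9% | 3.8–4.3% |
| 30/10 | 0.91 | 3.1% | 3.0–3.3% |

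At 10/30 the simulated true standard error is 0.494 s, while the model reports 0.442 s.

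**Step 4: the same donor assumption with repeated draws** (25 draws per trial, donor pool resampled before each, 1,500 runs).

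- *Rubin's rules:* power 94.7% (correlation 0.78) and 87.4% (0.70); type I error 3.3% at 10/30.
- *Averaged estimate with its repeated-sampling standard error:* power 98.3% and 95.6%. A bootstrap stratified by arm that repeats the donor step gave 4.8–4.9% type I error, including at 10/30.
- *For comparison, ANCOVA on completers only:* power 98.0% and 94.7%.

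**The case against.** Several points on the other side are sound.

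- **Direction of drop-out.** A reader might infer that controls will drop out more because their programme is less attractive, and hence that the test is anti-conservative. The protocol does not support this. It gives one 20% figure, informed by a single-arm feasibility study. Both arms get the same number of consultations, and information about the other arm is kept superficial to limit preference effects. The experimental arm carries the heavier burden (home exercises, a daily log, planning). Higher experimental drop-out is at least as plausible, and the test is then conservative. With equal 20% drop-out probability and chance imbalance allowed, type I error was 4.7%.
- **The word *conservative*.** A reader might call the claim false. Step 6 explains it as weakening the treatment effect, and that is true: 2.0 s becomes 1.6 s. What does not follow is that the test holds its 5% level.
- **Power.** A reader might infer that the trial is underpowered. It is not: the stated figures include the rule and reproduce.
- **Power gain from the remedy.** Averaging alone recovers almost none. The gain comes from choosing a repeated-sampling variance, which makes the test behave much like a completers-only test and so removes most of the penalty for drop-outs that the protocol accepted. That is a real trade-off.
- **Detail left to the analysis plan.** A seed could be fixed there. That makes the p-value reproducible but leaves it resting on one arbitrary draw. The one-draw rule itself is in the article.

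The dependence on the draw survives all of these, and it needs no unequal drop-out.

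**Conclusion.** The concern holds in a limited form. As written, the official test depends on a single random draw, and two draws disagree on significance in about 6% of trials at the planned assumptions, rising to 11–12% and 17% under the less favourable ones. Its standard error is correct only at equal drop-out: across the illustrated splits the type I error runs from about 3% to about 8%, and the protocol gives no basis for saying which side will apply.

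This is a weakness of the analysis rule, worth correcting before data exist. It is not an error in the sample size, and it does not show that the trial will be anti-conservative. The figures assume drop-out completely at random; bias from informative drop-out was not examined.

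**What to change.** Keep the control-change assumption and change its execution in the primary analysis, and likewise for the secondary endpoints:

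1. Repeat the random draw at least 100 times with a seed fixed in advance, and average the ANCOVA estimates. With 100 draws the draw noise falls to about 0.205/√100 = 0.02 s.
2. Pre-specify one variance that reflects both the imputation and the reuse of control donors. One option is Rubin's rules with the donor pool resampled before each draw: no inflation, power about as stated, somewhat conservative. The other is a bootstrap stratified by arm that repeats the donor step in every resample: about nominal error and higher power, but close to a completers-only test. Either is defensible; the choice must be made before unblinding.
3. In step 6 of the sample size section, limit the word *conservative* to the effect estimate.

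The cost is revised wording, a few hours of programming and output that is not the standard ANCOVA table. No patients or visits are added. Trial status reports that participant recruitment had not begun at submission, so the change could be made before any outcome data.
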